## Abstract

**Background**: Cancer-related cognitive impairment is a frequent and clinically relevant concern among women with breast cancer, particularly during active oncological treatment, with potential consequences for memory, attention, executive functioning, daily autonomy, emotional well-being, and quality of life. This study aims to evaluate the effectiveness of the Playful Attention and Active Memory intervention (ALMA) on cognitive functioning in women with breast cancer undergoing active oncological treatment. **Methods**: This single-centre, three-arm, parallel-group randomized controlled trial at the University Healthcare Complex of Salamanca (Spain) will evaluate 63 women with breast cancer undergoing active oncological treatment. Participants will be randomized (1:1:1) into a health education control group, an individual non-tailored cognitive training group, or the ALMA multidimensional group intervention (two 120 min face-to-face sessions/week for four months, combining psychoeducation, targeted cognitive stimulation, and group feedback). Assessments will occur at baseline and post-intervention. The primary outcome is objective global cognitive performance (Montreal Cognitive Assessment). Secondary outcomes include perceived cognitive function, everyday cognition, functional autonomy, anxiety, sleep quality, performance status, and everyday memory failures. Intention-to-treat analysis using linear mixed models will perform prespecified comparisons of ALMA versus both other groups. **Expected results**: This study is designed to provide evidence on the potential value of a structured, multidimensional cognitive intervention delivered during active breast cancer treatment. By comparing ALMA with both health education and individual cognitive training, the trial may clarify whether the integration of psychoeducation, ecological cognitive stimulation, and group-based support offers additional benefits beyond cognitive practice alone. The inclusion of objective, subjective, and functionally oriented outcomes strengthens the clinical relevance of the protocol and may contribute to the development of more comprehensive supportive care strategies for cancer-related cognitive impairment. Trial registration: This protocol is registered at ClinicalTrials.gov under the identifier NCT07165912.

## 1. Introduction

Breast cancer is among the most prevalent malignancies affecting women worldwide, representing a significant public health concern, particularly in Spain [1,2]. It is characterized by the uncontrolled growth of malignant cells in breast tissue, with the potential to invade surrounding structures and metastasize to distant organs [3]. Advancements in early detection and oncological treatment have led to improvements in survival rates, prompting a shift in clinical focus towards the short- and long-term consequences of cancer and its treatment [2,4,5]. Among these consequences, cancer-related cognitive impairment (CRCI), commonly referred to as “chemobrain,” has received increasing attention because of its potential impact on daily functioning, autonomy, emotional well-being, and quality of life [4,5,6,7,8,9].

Cancer-related cognitive impairment may involve difficulties in memory, attention, processing speed, executive functioning, and perceived cognitive efficiency [9,10,11,12,13,14,15]. These difficulties may occur during or after oncological treatment and may persist for months or years in some patients [11,14,15]. Current evidence suggests that CRCI has a multifactorial origin, involving treatment-related neurotoxicity, hormonal changes, inflammatory processes, fatigue, sleep disturbances, anxiety, emotional distress, and other psychosocial factors [12,16,17,18,19,20]. Although the severity and persistence of cognitive symptoms vary across patients, CRCI may interfere with instrumental activities of daily living, social participation, treatment self-management, and return to usual roles [4,19,20].

Non-pharmacological approaches, including cognitive training, cognitive stimulation, psychoeducation, and rehabilitation-oriented interventions, have been proposed as feasible strategies to address CRCI [21,22]. These interventions are designed to enhance cognitive functioning, promote compensatory strategies, and support patients’ perceived control over their daily cognitive challenges [21,22,23]. A recent series of systematic reviews indicates that cognitive rehabilitation and non-pharmacological interventions may improve in terms of cognitive and functional measures in adults diagnosed with cancer. However, the current evidence is characterized by significant heterogeneity in terms of intervention format, intensity, timing, outcome measures, and target population [23,24,25].

An important gap concerns the implementation of structured cognitive interventions during active oncological treatment, a period in which cognitive complaints, fatigue, emotional distress, and treatment-related disruption may be particularly relevant [4,18]. In addition, limited research has directly compared an individual cognitive training programme with a multidimensional group-based intervention combining psychoeducation, cognitive stimulation, and peer interaction. This comparison may help clarify whether the group-based and multimodal components provide additional benefits beyond individual cognitive practice alone [21,24,25].

The present protocol describes a three-arm randomized controlled trial designed to evaluate the Playful Attention and Active Memory intervention (ALMA) in women with breast cancer undergoing active treatment. The ALMA intervention combines psychoeducation, targeted cognitive stimulation, and group feedback, and will be compared with an individual non-tailored cognitive training programme and a health education control condition. The study will assess changes in objective global cognitive performance, perceived cognitive function, everyday cognition, functional autonomy, anxiety, sleep quality, performance status, and everyday memory failures. The inclusion of ecologically valid measures is intended to examine whether potential cognitive changes are reflected in everyday functioning.

The primary objective of this trial is to evaluate the efficacy of the ALMA group intervention in enhancing objective global cognitive performance in women with breast cancer undergoing active oncological treatment, in comparison with individual cognitive training and health education. The primary hypothesis is that participants allocated to the ALMA group intervention (G2) will show greater improvement in MoCA total score from baseline to post-intervention than participants allocated to the health education control group (G0). A second planned hypothesis is that participants allocated to ALMA (G2) will show greater improvement in MoCA total score than participants allocated to the individual cognitive training group (G1), reflecting the potential added value of the multidimensional and group-based components of the ALMA intervention.

## 2. Materials and Methods

### 2.1. Study Design and Setting

This prospective, longitudinal, randomized controlled trial aims to evaluate the efficacy of the ALMA cognitive intervention programme in addressing cancer-related cognitive impairment. The effects of ALMA will be compared with an individual cognitive training programme and a health education control group.

The trial design has been developed in accordance with the Standard Protocol Items: Recommendations for Interventional Trials (SPIRIT) 2013 guidelines [26]. This one-year clinical investigation will be conducted at the University of Salamanca (Spain), specifically within the Department of Medical Oncology at the University Healthcare Complex of Salamanca.

### 2.2. Participants and Eligibility Criteria

Recruitment will be initiated by a qualified oncologist at the University Healthcare Complex of Salamanca, who will identify potential candidates and provide preliminary information regarding the trial. If interested, patients will be scheduled for an in-person consultation with a member of the research team. During this session, the study’s objectives and procedures will be detailed, and any participant question will be addressed.

To determine final eligibility, screening assessment will be conducted. This process will include a baseline research protocol, including a battery of neuropsychological assessments and standardized questionnaires designed to evaluate sleep quality, anxiety symptomatology. Furthermore, written informed consent will be obtained from all subjects prior to any study-related procedures, in accordance with the Declaration of Helsinki.

A summary of the Initial Assessment Protocol and Anamnesis Phase is provided in Table 1. Potentially eligible participants will be identified consecutively and randomized after consent and baseline assessment.

Women aged 18 years and over who have been diagnosed with histologically confirmed breast cancer, at stages I–IV, and who are receiving active oncological treatment at the time of recruitment are eligible to participate. Active treatment will include chemotherapy, radiotherapy, and hormone therapy. Patients with metastatic disease will be included in the study. The time since diagnosis, disease stage, recurrence status, metastatic status, and treatment modality will be recorded as clinical variables rather than used as restrictive eligibility criteria. The specific inclusion and exclusion criteria are described in Table 2 and detailed below:

### 2.3. Recruitment

Participants will be recruited from the Department of Medical Oncology at the University Healthcare Complex of Salamanca. Consecutive identification of potentially eligible women by the oncology team during routine clinical care is to be conducted in accordance with the predefined inclusion and exclusion criteria. Patients who appear to meet the initial eligibility criteria will receive preliminary verbal information about the study. If they express interest, they will be referred to a member of the research team for a detailed explanation of the trial procedures.

The estimated recruitment period will be 12 months, or until the target sample size of 63 participants has been reached. A screening log will be maintained to document the number of patients assessed for eligibility, excluded before randomization, reasons for exclusion when available, number of patients who decline participation, and number of participants randomized to each study arm.

In the event that the intended sample size is not attained within the anticipated recruitment period, the research team may opt to extend the recruitment period, enhance coordination with the oncology service, augment the frequency of screening of outpatient clinic schedules, and provide additional information sessions to eligible patients. Any substantial change in the recruitment strategy, recruitment period, or study setting will be submitted to the Research Ethics Committee for approval when required and will be updated in the trial registry where applicable.

Refusal to participate or withdrawal from the study will not affect participants’ usual oncological care or their relationship with the clinical team.

### 2.4. Sample Size

The planned sample size for this trial is 63 women with breast cancer undergoing active oncological treatment, with 21 participants allocated to each of the three study arms: health education control group (G0), individual cognitive training group (G1), and ALMA group intervention (G2).

The sample size calculation was based on the primary outcome, defined as the change in objective global cognitive performance from baseline (T0) to post-intervention (T1), assessed using the Montreal Cognitive Assessment (MoCA). As no directly comparable previous trial evaluating the ALMA intervention in women with breast cancer was available, the expected effect was estimated using an indirect reference study that evaluated a multicomponent cognitive stimulation programme and reported a mean post-intervention increase of 2.95 points in MoCA score [27]. Assuming a common standard deviation of 3.48, this corresponded to an estimated standardized effect size of Cohen’s d ≈ 0.85.

For the purposes of sample size estimation, this effect was converted to an approximate ANOVA effect size of f ≈ 0.40. The calculation was performed using G*Power software, version 3.1.9.7 [28], for a balanced one-way fixed-effects ANOVA with three independent groups, an alpha level of 0.05, statistical power of 80%, and equal allocation across groups. Under these assumptions, a minimum total sample of 57 participants was required to detect an overall between-group difference.

To account for an anticipated attrition rate of approximately 10%, the recruitment target was increased to 63 participants, corresponding to 21 participants per study arm. This inflation is intended to preserve statistical power for the primary analysis under the intention-to-treat principle.

Although the primary effectiveness analysis will be conducted using linear mixed models to evaluate the Group × Time interaction across baseline and post-intervention assessments, the ANOVA-based sample size calculation was used as a conservative and transparent approximation for planning purposes. Linear mixed models are expected to make efficient use of repeated-measures data and to accommodate missing outcome data under the missing-at-random assumption. Therefore, the ANOVA-based calculation was considered appropriate for estimating the minimum feasible sample size while maintaining consistency with the planned three-arm randomized design.

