#### 2.6.2. Cognitive Training Group (CT) G1

Participants in the Cognitive Training (CT) group (G1) will undergo a structured programme focused on everyday cognition, administered individually to each patient. The intervention will be delivered through a meticulously developed dossier designed specifically for the objectives of this study. Notably, all participants in this arm will receive identical tasks, with no individualized adaptations for difficulty level or functional profile.

The intervention is structured into four consecutive one-month training periods (P1–P4), totaling 80 activities (20 activities per period). Participants are required to complete five activities per week. To monitor treatment adherence and ensure compliance with therapeutic guidelines, a dual follow-up system will be implemented:Remote Follow-up: Conducted via video call at the conclusion of P1 and P3 (Months 1 and 3).In-person Follow-up: Conducted at the clinic at the conclusion of P2 and P4 (Months 2 and 4) to evaluate progress and address emergent concerns.

The final evaluation for G1 will coincide with the completion of the fourth training period (P4). This group serves to control the effects of cognitive stimulation and professional monitoring without the specific multimodal components of the ALMA.

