### 3.2. Primary Outcome: Objective Global Cognitive Performance

The primary endpoint will be the between-group difference in change in MoCA total score from baseline (T0) to post-intervention assessment (T1), calculated as ΔMoCA = MoCA score at T1 − MoCA score at T0. The MoCA is a brief standardized cognitive screening instrument that evaluates multiple cognitive domains, including executive functions, attention, abstraction, memory, calculation, language, visuospatial abilities, and orientation. The total score ranges from 0 to 30, with an administration time of approximately 10–12 min. To correct for socio demographic educational bias, an additional point is added to the total score for participants with ≤12 years of formal education. The Spanish version exhibits robust psychometric validity, with a reported internal consistency of Cronbach’s α = 0.84 and a test–retest reliability of r = 0.92. A score below the clinical cut-off of <26 points indicates objective cognitive impairment. For cancer-related cognitive impairment (CRCI) monitoring, the Minimal Detectable Change (MDC) is established at ±2 points; thus, an intra-subject post-intervention increase of ≥2 points indicates a true, statistically stable cognitive improvement.

In this study, the MoCA will be used as an objective global measure of cognitive functioning rather than as a diagnostic tool for cancer-related cognitive impairment [30].

Although CRCI may involve subtle and domain-specific cognitive changes, the MoCA was selected as the primary outcome because it provides a standardized, feasible, and clinically interpretable measure of global cognitive performance. To complement this global measure, secondary outcomes will include patient-reported cognitive functioning, everyday cognition, functional autonomy, sleep quality, anxiety, performance status, and everyday memory failures.

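### The planning effect is described as a post-intervention MoCA increase but used as a between-arm difference, with nothing allowed for change in G0 or G1, so the stated 80% power is not supported for the primary endpoint

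*Protocol article*

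**What the plan says.** Section 2.4 (Sample Size) takes its effect from an indirect reference study of a multicomponent cognitive stimulation programme, which "reported a mean post-intervention increase of 2.95 points in MoCA score". It continues: "Assuming a common standard deviation of 3.48, this corresponded to an estimated standardized effect size of Cohen’s d ≈ 0.85". Then "this effect was converted to an approximate ANOVA effect size of f ≈ 0.40", which goes into a one-way ANOVA with "three independent groups, an alpha level of 0.05, statistical power of 80%, and equal allocation across groups". The result is that "a minimum total sample of 57 participants was required to detect an overall between-group difference", raised to 63 for dropout.

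Section 3.2 defines the endpoint: "The primary endpoint will be the between-group difference in change in MoCA total score from baseline (T0) to post-intervention assessment (T1"). Section 3.9 tests it as two Holm-adjusted contrasts, G2 (ALMA) versus G0 and G2 versus G1.

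No section gives an expected MoCA change for G0 or G1. Section 2.6.1 presents G0 as showing the natural course under standard care. Section 2.6.2 says of G1: "This group serves to control the effects of cognitive stimulation and professional monitoring without the specific multimodal components of the ALMA".

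**The concern.** A post-intervention increase in treated patients and a difference between arms in change are different quantities. The first contains whatever would have happened without the programme: retest gain, regression to the mean, and the course of the disease and its treatment. The second has that removed by subtraction. All three arms take the MoCA at T0 and T1, so G0 and G1 can also change.

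G1 raises a further question. It delivers 80 cognitive activities and is meant to carry the effect of stimulation. The gain seen under a stimulation programme cannot simply be credited to ALMA over G1.

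The denominator is also undefined. The endpoint is a change score, so the SD that matters is the SD of change (or a baseline-adjusted residual SD). Section 2.4 calls 3.48 a common SD without saying of what.

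At stake is the one figure that justifies 63 women. If it does not describe the primary endpoint, a non-significant result, above all for G2 versus G1, would be read against a power that the plan has not shown.

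**Working it through.** **Inputs from the protocol article.** Effect 2.95 points, SD 3.48, f ≈ 0.40, three arms, alpha 0.05, 57 evaluable women (19 per arm), 63 recruited (all Section 2.4); MoCA test–retest r = 0.92 (Section 3.2).

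**Assumptions, not in the document.** The mean changes in G0 and G1, and the T0–T1 correlation over four months of active treatment.

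**Step 1: the plan's own effect size.** d = 2.95 / 3.48 = 0.848, as stated. For three arms, f is the SD of the three mean changes (divisor 3) over the common SD. With mean changes G0/G1/G2 of 0, 0 and 2.95, f = 0.848 × √2 / 3 = 0.400. The same f results from 0, 2.95 and 2.95. With G1 midway (0, 1.475, 2.95), f = 0.848 / √6 = 0.346. So f ≈ 0.40 corresponds to the whole 2.95 being the gap between G0 and G2, with G1 equal to one of them.

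**Step 2: power at 57 under that pattern.** Noncentral F with λ = N·f² and 2 and N − 3 degrees of freedom. λ = 57 × 0.3996² = 9.10, giving power of 75%. With all 63 evaluable it is just under 80% (79.7%). The shortfall from 80% at 57 is a separate matter: 57 does not follow from f = 0.40. It is only the starting value here.

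**Step 3: let the comparators change.** G0 and G1 change equally, ALMA gains 2.95, SD of change 3.48, N = 57.

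| Change in G0 and G1 (assumed) | Net difference | f | λ | Power |
|---|---|---|---|---|
| −0.5 | 3.45 | 0.467 | 12.45 | 88% |
| 0 | 2.95 | 0.400 | 9.10 | 75% |
| +0.5 | 2.45 | 0.332 | 6.28 | 58% |
| +1.0 | 1.95 | 0.264 | 3.98 | 39% |

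The effect of this point alone is the movement away from 75%: down 17 percentage points for a half-point gain, down 36 for a one-point gain, up 13 for a half-point decline. With G1 midway between G0 and ALMA, and G0 at 0, +0.5 and +1.0, power is 62%, 46% and 30%.

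**Step 4: let the SD vary.** If 3.48 is an SD of scores, equal at both visits, the SD of change is 3.48 × √(2(1 − r)). It equals 3.48 only at r = 0.5. Power at N = 57 with equal gains in G0 and G1:

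| r (assumed, except 0.92) | SD of change | Gain 0 | Gain 0.5 | Gain 1.0 |
|---|---|---|---|---|
| 0.3 | 4.12 | 60% | 44% | 29% |
| 0.5 | 3.48 | 75% | 58% | 39% |
| 0.7 | 2.70 | 93% | 81% | 60% |
| 0.92 | 1.39 | >99% | >99% | 99% |

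The 0.92 is a reliability coefficient for the instrument. Section 3.2 does not offer it as the correlation across four months of treatment, so it marks one end of the range.

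**The case against.** The strongest reply has four parts.

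*The source's design is not shown.* The article does not say whether the reference study had a control arm, and a common SD is two-group language. A reader might infer that 2.95 is certainly a one-arm before–after gain. The document does not establish that; it only describes the figure as an increase and subtracts nothing. This part stands, so the remedy must ask what the figure is.

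*Comparators may decline.* G0 is observed during active treatment, and the Discussion cites up to 75% of patients with cognitive alterations in that period. A decline in G0 widens the gap. This also stands. It would be tempting to say that the 80% holds only if G0 stays still and G1 behaves like G0 or ALMA. That condition is not sufficient (75% at 57) and not necessary (88% if G0 and G1 fall by 0.5 points).

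*The SD may be smaller.* A high T0–T1 correlation would more than offset a modest comparator gain. This stands, so the documents do not show that the trial is underpowered. They show that its power is undetermined.

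*Section 2.4 sizes only an overall difference and admits an indirect source.* It does not assign 2.95 to G2 versus G1, so the plan cannot be accused of assuming that G1's training does nothing. But admitting that a source is indirect does not turn an increase into a difference between arms, and the overall test still needs three expected changes, which are not given.

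None of this supplies the missing subtraction or defines the SD.

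**Conclusion.** The point holds in this form: Section 2.4 uses a quantity described as a post-intervention increase as the between-arm effect, gives no expected change for G0 or G1, and leaves the SD undefined. The single 80% is therefore not supported for the endpoint in Section 3.2.

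At an SD of change of 3.48 and 57 evaluable women, power ranges from 39% to 88% across comparator changes from a 1.0-point gain to a 0.5-point decline. These figures rest on ALMA gaining exactly 2.95, G1 changing like G0, and the overall F test. The direction of the error is not known, because a decline in the comparators or a smaller SD of change would restore or exceed 80%.

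The mismatch between 57 and f = 0.40, and sizing on an overall test when two contrasts are analysed, are separate points. Correcting either would leave this input unchanged.

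**What to change.** Keep 63 women. In Section 2.4:

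1. State whether 2.95 is a within-group increase or a between-arm difference in the reference study, and whether 3.48 is an SD of scores or of change.
2. Restate the planning effect as the net difference in MoCA change, separately for G2 versus G0 and G2 versus G1. Standardise it by the SD of change, with the T0–T1 correlation stated.
3. Replace the single 80% with the power and the minimum detectable net difference for each planned contrast, over a range of comparator changes on both sides of zero (decline, none, gain).
4. Say that a non-significant G2 versus G1 result does not show equivalence.

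Do not take the 2-point minimal detectable change in Section 3.2 as the between-arm target. It is defined within a patient, and using it between arms would repeat the same confusion.

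The cost is one rewritten section and a short table. No patients, visits or tests are added. The downside is a stated power that is less favourable, or a wide range.
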